#### Data sources/measurement

A customized eCRF (electronic Case Report Form) was created for the study. Each local investigator will be responsible to ensure that the eCRFs is thoroughly filled in. Study data will be collected and managed using REDCap electronic data capture tools hosted at Fondazione Policlinico Universitario A. Gemelli, IRCCS (https://redcap-irccs.policlinicogemelli.it/) provided by the Research Core Facility DATA COLLECTION of the Science and Technology Park of Fondazione Policlinico Universitario A. Gemelli IRCCS (GSTeP). REDCap (Research Electronic Data Capture) is a secure, web-based application designed to support data capture for research studies, providing:An intuitive interface for validated data entry;Audit trails for tracking data manipulation and export procedures;Automated export procedures for seamless data downloads to common statistical packages;Procedures for importing data from external sources [36–39].

Only users registered as study investigators or data managers will receive a user login to access the REDCap web platform and enter/manage data. CRFs must be completed for all patients who have given informed consent. Sources of information are the physician’s patient record, hospital notes, original laboratory records, pharmacy records, and results of pathological examination. Data will be entered into the eCRF in a truthful, accurate, and timely manner.

To guarantee the highest safety and quality of data collection and management, the following were implemented:RedCap was installed in GDPR compliance including database encryption and meets several security policies and user needs including compliance with 21 CFR Part 11, FISMA, HIPAA.

A two-step authentication login process has been implemented (in addition to username and password, a temporary password, sent by mail, to access the system is required);2.The eCRF was built and will be managed according to ACCIT (Accuracy, Consistency, Completeness, Integrity and Timeliness) criteria [38, 39]. All tricks to improve data quality have been included by design such as calculated field, branching and skip logic, alert related to specific condition, and units conversion;3.Only pseudo-anonymized data will be collected. Each center will be identified with a unique code and a progressive number will be automatically attributed by REDCap to each patient enrolled. More in depth:The progressive transplant number in each center (not of the patient) and the day of the transplant will be collected.The name and the surname of the patient are not recorded. However, for the convenience of the center’s operators, the first two initials of the surname and name could be optionally reported to facilitate the identification of the case during the postoperative follow-up. These initials will be visible only to the operators of the center.4.Each center will only have access to their data. Only two operators/center can access the eCRF, one junior and one senior. Either the junior or the senior can enter and modify the records. The senior operator has two additional features:Records lock after validation (it can be done in a case-by-case mode or at the end of the study according to center preference);Dataset export for statistical analysis and other purposes;

NB: only de-identified data of its own center can be downloaded. De-identification allows limiting the amount of sensitive information that can be exported out of the project including one or more of the following:Removing all tagged Identifier fields (tagged in Data Dictionary), unvalidated Text fields (e.g., text fields other than dates, numbers), Notes/Essay box fields.Hashing the Record ID field (converts record name to an unrecognizable value).Removing date and date time fields or shifting all dates by value between 0 and 364 days (shifted amount determined by algorithm for each record).

#### Potential sources of bias and pre-identified solutions

center participation on a voluntary basis.

Issue: some centers might withdraw their participation.

Solution: a large number of centers was planned to accommodate potential withdrawals.2.Prospective cohort composed only by high-volume centers.

Issue: enrollment from high-volume centers might cause a loss of real-life description of the LT community situation.

Solution: only high-volume centers allow the collection of the required data to build new predictive models in a timely fashion. In addition, perfusion machines are utilized more commonly in high-volume centers. Nevertheless, data from medium-to-low volume centers will be used to validate the novel predictive model and the applicability to their clinical practice.3.Delayed enrollment.

Issue: some high-volume centers might experience a reduction in their LT activity for various reasons.

Solution: granting extension to allow the centers to meet their enrollment expectation, up to 6 months extra.4.Different prevalence of graft subtypes.

Issue: despite the efforts to balance the numerosity of the various LT subgroups, the number of DBD grafts remains higher than that of LD and DCD.

Solution: the preliminary sample size/power analysis calculation demonstrated that the planned enrollment allows sufficient numerosity to reveal the difference in the incidence of allograft failure at 90 and 365 days after LT.

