## Methods

### Study design, steering committee, and participating centers

This is a multicenter, international, non-competitive, observational two-segment study.

The study segments include a first one with retrospective patient enrollment and a second one with prospective enrollment (Table 3).

**Table 3 Tab3:** Study design and population

	Prospective segment (high-volume centers ≥ 65 transplants per year)	Retrospective segment (low- & intermediate- volume centers < 65 transplants per year)
Sample size	750	4200
Consecutive pts to be included	50	75
No. of Centers to be involved	15	56
Enrollment period	July ‘21–December ‘23	January ‘17–December ‘19
Data entry period	Up to January’25 (follow-up)	Up to October’24 (follow-up)
AIMs	Development/validation of NEW/previous prognostic algorithms	Validation of previous kinetic algorithms
Main parameters	AST, PLT, BIL, INR	AST, PLT, BIL, INR
Outcome data and follow-up	Incidence of AF at 90 and 365 days Comprehensive complication index Length of stay in ICU, length of stay in hospital 90d and 365d graft survival, 90d and 365d patient survival, 90d and 365d ischemic cholangiopathy-free survival Actuarial data at 12 months	Incidence of AF at 90 and 365 days Comprehensive complication index Length of stay in ICU, length of stay in hospital 90d and 365d graft survival,90d and 365d patient survival, 90d and 365d ischemic cholangiopathy-free survival Actuarial data at 48 months
Pre-operative assessment	Yes	No
Sarcopenia		Yes
Malnutrition		Yes
Cardiac risk		Yes
Renal risk		Yes
Biopsy of the graft (back table)	DBD, DCD	Only when available
Post-operative assessment of factors that favour or contraindicate re-transplant	Yes	No
Number of parameters to be recorded	297	241
Number of calculated fields	27	24

Prospective and retrospective segments

A steering committee (SC) was constituted to design the study (Fig. 1). Members were identified according to their experience on the topic and their geographic area (Europe, Americas, and Asia).

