**Fig. 3 Fig3:**
[figure not shown]
Rank of countries according to liver transplant activity and rank of enrolled transplants

The study will be structured in two segments, based on the enrollment modality: prospective and retrospective. Two distinct data collections will be created accordingly.Prospective segment. Seven hundred fifty liver transplant recipients will be enrolled in 15 high-volume centers (defined as performing ≥ 65 LT a year on average during the 2017–2019 period). Each center will enroll 50 consecutive transplants from July 2021 to December 2023 according to the inclusion criteria. For each transplant, a further 365 days will be necessary for the minimum follow-up.Retrospective segment. A retrospective data collection was conceived for medium–low volume centers (defined as performing < 65 LT a year), to participate in the study using the data of LTs performed between December 31, 2019, and January 1, 2017 (75 cases backward enrollment).

High-volume centers participating in the prospective segment will be allowed to enroll patients in the retrospective segment, too, voluntarily, thus enrolling 125 transplants (50 prospective and 75 retrospective transplants).

Inclusion and exclusion criteria are depicted in Table 4.

**Table 4 Tab4:** Inclusion and exclusion criteria

Inclusion criteria
1. Adult cases (≥ 18 years) 2. First transplant (retransplants to be enrolled when first transplant enrolled) 3. DBD grafts 4. DCD grafts (controlled and uncontrolled) 5. DBD and DCD grafts managed by perfusion machines 6. Living donor grafts (both left lobe and right lobe grafts) transplanted into adult recipients 7. Split liver grafts (both left lobe and right lobe grafts) transplanted into adult recipients
Exclusion criteria
1. Combined grafts (e.g., liver-kidney, liver-heart, liver-pancreas, multi-visceral grafts) 2. Domino grafts 3. Heterotopic grafts 4. Double grafts 5. Cholangiocarcinoma 6. Colorectal liver metastases

Due to some concerns regarding the differences in the prevalences of AB0 incompatible grafts among different countries, these patients can be enrolled concurring to the target number of cases for each center. During the statistical analysis, we will evaluate the opportunity to include them or not in the study population, being aware of the substantial equivalence in the survival results

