### Outcome measures

Allograft failure (AF) was defined as graft failure (leading to retransplant or death) for any reason at day 90 and at day 365 after LT. This definition also captures all late-occurring AFs (also known as delayed non-function) [34, 35] We consider as AF determinants all those events potentially affecting the process of graft function recovery, independently if they were strictly associated with ischemia–reperfusion injury. Indeed, vascular (thrombosis of the hepatic artery or portal vein), biliary, toxic, and major hemodynamic events will be included, because any of them can interact with parenchymal dysfunction, affecting graft function recovery and favoring graft failure and death.

Other outcome measures are comprehensive complication index, intensive care unit length of stay, hospital length of stay (LoS), and cholangiopathy-free survival at 90 and 365 days, graft and patient survival at 90 and 365 days,

The prospective cohort dataset includes 297 data entries and 27 calculated parameters (see supplementary material 1). Variable domains are:identification datadonor characteristics datarecipient preoperative datagraft histology dataintraoperative datarecipient postoperative datastudy endpoints dataoutcome and follow-up data.

The electronic Case Report Form (eCRF) was developed using the REDCap ver 10.0.21 software hosted at https://redcap-irccs.policlinicogemelli.it/. The eCRF allows easy calculation of scores including L-GrAFT and EASE scores.

The REDCAP software performs de-identification and encryption of the data.

The retrospective segment dataset includes 241 variables (supplementary material) to be collected from each center’s previously existing databases.

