Finally, the balanced data enrollment (each center in the prospective or retrospective segment will enroll a fixed number of cases) constitutes the best solution to minimize the center-volume effect bias.

The predictive models we aim to develop would also be tailored to the changing composition of the donor pool, with an emphasis on DCD, ECD, and possible risk-mitigation strategies. Such strategies, mainly machine perfusion (MP) but also minimizing donor hepatectomy time, warm and cold ischemia time, are heterogeneously implemented in the participating centers. This will also describe the current management options and provide a snapshot of the differences in clinical practice across the centers. Since the study enrollment encompasses 7 years, including 2 years of variable LT activity due to the COVID-19 pandemic, the growing adoption of MP translates into more frequent usage in the prospective study segment. This potential bias will be taken into account in all the statistical analyses. As MP for DCD and risky DBD grafts keeps gaining momentum and more trials are coming, our study will parallel the evolving scenario of graft reconditioning and extended preservation. Differently from most studies, [61, 62], we expect to enroll more DCD and DBD cases treated with MP in both study segments. Furthermore, the global perspective of the study will allow for a deeper analysis of the mitigation effect of MP, also about center volume. Nevertheless, we are aware that since this study remains observational, novel experimental procedures such as MP-based pharmacological defatting [63] will not be incorporated.

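### Counted from December 2023, the six-month enrollment extension leaves late prospective transplants without complete 365-day data by the January 2025 close of data entry

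*Protocol article*

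**What the plan says.** Four statements in the protocol article set the prospective timeline.

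- **Enrollment window.** Table 3 (Study design, steering committee, and participating centers) gives "July ‘21–December ‘23". The Setting section agrees: "Each center will enroll 50 consecutive transplants from July 2021 to December 2023 according to the inclusion criteria".
- **Minimum follow-up.** The Setting section adds: "For each transplant, a further 365 days will be necessary for the minimum follow-up".
- **Close of data entry.** Table 3 gives the prospective data-entry period as "Up to January’25 (follow-up").
- **Extension.** Item 3 of Potential sources of bias and pre-identified solutions foresees that "some high-volume centers might experience a reduction in their LT activity for various reasons". The solution is "granting extension to allow the centers to meet their enrollment expectation, up to 6 months extra". High-volume centers are the ones that make up the prospective segment.

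The outcome that needs the whole follow-up is allograft failure (AF), defined in Outcome measures as "graft failure (leading to retransplant or death) for any reason at day 90 and at day 365 after LT". Prediction at both time points is primary objective #2 in Table 2.

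Nothing in the text shown moves the data-entry close for a center granted an extension, limits the extension to what the close permits, or says that December 2023 already contains it.

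**The concern.** The January 2025 close matches the unextended window with about a month to spare. An extension of up to six months is far longer than that margin, so the contingency offered for slow enrollment appears to undercut the minimum follow-up stated for every transplant.

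At stake is the completeness of the 365-day outcomes for late-enrolled cases. Two items are exposed: AF status at day 365 when it is used as a yes/no outcome, and any cholangio-MR due at 10–12 months. The lost months also matter clinically. The Introduction places ischemic cholangiopathy typically at 6–12 months, and the Discussion says that evaluation was extended to 365 days to capture later failures. The affected cases would come from centers that needed the extension, for which the article's stated reason is reduced activity, so they would not be a random subset of the segment.

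**Working it through.** **Inputs**

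- End of prospective enrollment: December 2023, taken as 31 December 2023 (Table 3; Setting).
- Minimum follow-up: 365 days (Setting).
- Close of prospective data entry: January 2025, taken as 31 January 2025, the latest and most favourable reading (Table 3).
- Extension: up to 6 months. Assumption: it runs from the end of December 2023, so it ends on 30 June 2024.
- Center volume and target: at least 65 transplants a year, and 50 consecutive cases per center (Setting; Table 3).

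**Step 1. Reproduce the plan's own dates.** Day 365 = transplant date + 365 days. For the last unextended transplant, 31 December 2023 + 365 days = 30 December 2024. That is 32 days before 31 January 2025, so the base timeline is consistent.

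**Step 2. Add the extension.**

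| Last transplant | Day 365 | Days past 31 Jan 2025 | Follow-up available at close |
|---|---|---|---|
| 31 Dec 2023 (no extension) | 30 Dec 2024 | −32 | 397 days |
| 31 Jan 2024 | 30 Jan 2025 | −1 | 366 days |
| 31 Mar 2024 | 31 Mar 2025 | 59 | 306 days |
| 30 Jun 2024 (full extension) | 30 Jun 2025 | 150 | 215 days |

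**Step 3. Find the cut-off date.** 31 January 2025 − 365 days = 1 February 2024. If entry closed on 1 January 2025, the cut-off would be 2 January 2024. On the favourable reading, roughly the first month of an extension still fits and about five of the six months do not.

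**Step 4. See which outcomes are touched.** For a transplant on 30 June 2024, day 90 is 28 September 2024, well before the close, so all 90-day outcomes are complete. For the imaging, 31 March 2024 plus ten calendar months is 31 January 2025. Transplants after about the end of March 2024 would therefore not reach the start of the 10–12 month window by the close.

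**Step 5. Ask how likely the overrun is.** At 65 transplants a year, 50 cases take 50 / 65 × 12 = 9.2 months. The base window, July 2021 to December 2023, is 30 months or 2.5 years. A center enrolling throughout overruns it only if it averages fewer than 50 / 2.5 = 20 cases a year, which is 20 / 65 = 31% of the volume threshold. Otherwise it would have to start late.

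**The case against.** The strongest reply is that the conflict depends on two premises the article does not state outright. First, the extension has no anchor date, and December 2023 may already include it. The Discussion says "Since the study enrollment encompasses 7 years", which equals January 2017 to December 2023, and a 30-month window for about nine months of work already looks generous. Second, January 2025 is a planned data-entry period, not a declared database lock. Data sources/measurement lets centers lock records case by case or at the end of the study and gives no calendar date. A center with an extension might be expected to complete 365 days per case and enter data later. The GANTT diagram (Fig. 2) is not in the text available and might show which is meant.

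This stands in part. A reader might infer that the follow-up, extension and closing statements cannot all be true. The documents do not support that, because the reading in which December 2023 includes the extension removes the conflict. But the article never says so, and the seven-year span fits equally well with no extension having been counted. On the plain reading the dates conflict, and they are dates the article itself fixes, not detail left to another document.

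Two further inferences should be resisted. One is that a sizeable share of the 750 patients would be affected: nothing in the article says how many centers would use the extension or how many cases they would place in it, and Step 5 points to few. The other is that late failures would be under-counted. That follows only if patients with incomplete follow-up are classed as non-failures, which the article does not say. The planned Kaplan–Meier and Cox analyses can censor such patients at the close, and losses are to be reported with the numbers at risk. The cholangio-MR is on demand, so only some affected patients would have imaging due.

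Censoring does not supply a day-365 status where the outcome is handled as a proportion or a yes/no label, nor an imaging result that falls after the close. That much of the concern survives.

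**Conclusion.** The point holds as an inconsistency in the timeline, of minor importance. With the extension counted from December 2023 and data entry closing no later than 31 January 2025, prospective transplants after about 1 February 2024 could not have complete 365-day data, and the shortfall reaches 150 days for a transplant on 30 June 2024. It is confined to 365-day outcomes in centers that use more than about the first month of the extension. The number of patients cannot be derived from the article and is probably small. The conclusion rests on the anchor date assumed for the extension and on reading January 2025 as the actual end of data entry. If either is meant differently, the remedy reduces to saying so.

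**What to change.** Reconcile Table 3, the Setting section and item 3 of the bias section in one of three ways:

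1. Close prospective data entry no earlier than 365 days, plus time for entry, after the last enrolled transplant. For a full extension this means 30 June 2025 at the earliest, or about the end of July 2025 with the present one-month margin.
2. Keep the January 2025 close and cap the extension so that day 365 falls before it, which means a last transplant no later than about 1 February 2024.
3. If December 2023 was meant to include the extension, state that.

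The first option moves the lock by up to about five months, or about six if the one-month margin is kept, and only if the extension is fully used. The second may cost a few cases in a few centers. The third costs one sentence.

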#### Study size and power calculations

The study size was calculated to achieve adequate statistical power for the development and validation of prognostic algorithms. Calculations were independently performed by the G-Step Statistical Facility of the Fondazione Policlinico A. Gemelli IRCCS.

*1. Prior knowledge*

1.1. AF incidenceIncidence of allograft failure (AF) at 90 days according to the L-GrAFT study (2018): 11.1% [1].Incidence of AF at 90 days according to the EASE score study: 6.7% [2]—Incidence of EAF according to the L-GrAFT validation study (2020) in UCLA: 7% [17].Incidence of AF at 90 days according to the L-GrAFT validation study (2020) in other US validation centers: 11% [17].Incidence of AF at 90 days according to the L-GrAFT validation study (2020) in European COPE cohort: 4% [17]. Notably, the COPE cohort consists of 222 grafts.

Research hypothesis stratified by donor category:10% AF in liver transplantation with high-risk deceased donors;7% AF in liver transplantation with standard deceased donors;4% AF in liver transplantation with living donors.

1.2. EASE and L-GrAFT score performance as AUC (95% confidence interval)EASE(10) AUC = 0.87 (0.83, 0.91).L-GrAFT10 AUC = 0.72 (0.65, 0.78).L-GrAFT7 AUC = 0.78 (0.75, 0.82).

*2. L-GrAFT and EASE score algorithms validation*

Current target sample size (*n*):5000 transplants overall;> 4125 for the retrospective study.750 for the prospective study.

This estimation aims to provide the minimum sample size to achieve the baseline AUC, considering a different AF incidence for each donor category. The baseline (i.e., lowest) AUC = 0.72 of the L-GrAFT10 score is considered a minimum performance requirement to reach a conservative sample size estimation.

Assuming an overall AF rate of 6% and aiming to exclude an AUC value of 0.72, a minimum sample size of 4000 patients will result in a 95% confidence interval width of 0.072; so, if we obtain an AUC of at least 0.76, the 95% confidence interval, ranging from 0.724 and 0.796, will allow to exclude the value of 0.72.

*3. Dimension of the validation set.*

The validation set (prospective segment) will consist of 750 patients. This sample size was calculated according to Riley et al. [40] to obtain an acceptable calibration-in-the-large based on O/E, which is the ratio of the total number of observed outcome events, divided by the total number of expected (predicted) outcome events. Assuming an AF incidence rate of 0.06, 800 patients will allow to estimate an expected O/E equal to 1 with a Standard Error in log-scale of 0.14; this target will translate in a 95% confidence interval for the incidence rate ranging from 0.043 to 0.077.

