 Timely prediction of AF is pivotal to identifying patients who may potentially benefit from a rescue retransplant before severe complications develop. When massive cytolysis and clear signs of liver failure occur within the first 2–4 days after LT, the indication for retransplantation is clear. Diversely, the decision to retransplant a patient with a milder degree of AF (also called dysfunction) is more challenging, especially after the first 5–10 postoperative days. AF results from a complex interplay between donor, procurement-related, and recipient perioperative factors, all of which contribute to the severity of the ischemia–reperfusion injury. Conversely, the ability of an allograft to recover from such injury is similarly impacted by numerous perioperative events (e.g., preoperative cardiac ischemic damage, frailty–sarcopenia, graft rejection, drug toxicity, kidney failure, or sepsis), [23–31] many of which are poorly studied. Although L-GrAFT and EASE scores accurately predict AF with excellent discrimination, these existing models have not specifically elucidated the role of perioperative events on the need for retransplantation [1, 2, 17]. Notably, this literature is exclusively based on retrospective, single-center studies which have not considered the center-volume effect, with a limited number of DCD and ECD grafts and no evaluation of the possible mitigation effect of MP technologies [1, 2]. The IMPROVEMENT project was designed to pay particular attention to these shortcomings, to capture and analyze as many of these qualitative and semi-quantitative variables as possible to build a comprehensive model that may meaningfully predict AF and guide treatment decisions regarding retransplantation. The study objectives are detailed in Table 2.

**Table 2 Tab2:** Study objectives

Primary (#1)	To make a snapshot of the liver transplant activity on a global basis
Primary (#2)	To develop new algorithms for the timely prediction of Allograft Failure at 90 and 365 days using a comprehensive prospectively collected dataset based on the current clinical practice of liver transplant centers
Secondary (#3)	To validate the already existing predictive models and the newly developed algorithms on a retrospective cohort of patients from intermediate to high medium-volume transplant centers;
Secondary (#4)	To develop a novel time-based dynamic algorithm, with increasing accuracy from the 3^rd^ to 7^th^ post-operative day;

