### Setting

The study will be conducted in 60 (or more) liver transplant centers representative of the global liver transplant activity (Fig. 2). The Italian liver transplant population constitutes the primary study population, while the other geographic areas (Europe without Italy, Asia, Oceania, and North and South America) will be used as a comparator. Instead, for the development of the main algorithms, the study population will be utilized as a whole.

Since the study aims to reflect the worldwide liver transplant activity, to balance each country contribution in the study, we used the proportions of LT activity as reported on the Global Liver Transplant Observatory [32]. This ranks the yearly number of transplants performed in various countries in decreasing order. A stratification of all cases in five classes based on quintiles was provided to parallel the number of centers to be recruited in each country. For countries in the 4^th^ and 5^th^ quintile classes, one or two centers are allowed, coherently with the 75 cases per center rule (Fig. 3), as per participation in the “Retrospective segment” of the study. Countries with < 50 cases per year are not considered.

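### The protocol gives the prospective segment conflicting roles for the new prediction model, and neither sample-size calculation covers model development

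*Protocol article*

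**What the plan says.** The article describes the data for the new model in several places.

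- **Prospective segment as validation set.** Study size and power calculations, item 3: "The validation set (prospective segment) will consist of 750 patients". The only criterion there is calibration-in-the-large, through the observed/expected (O/E) ratio.
- **Prospective segment as development set.** Table 2, primary objective #2: "To develop new algorithms for the timely prediction of Allograft Failure at 90 and 365 days using a comprehensive prospectively collected dataset". The section on potential sources of bias gives the reason: "only high-volume centers allow the collection of the required data to build new predictive models in a timely fashion".
- **Retrospective segment as validation set for the new model.** Table 2, secondary objective #3: "To validate the already existing predictive models and the newly developed algorithms on a retrospective cohort of patients". The bias section agrees: "data from medium-to-low volume centers will be used to validate the novel predictive model".
- **Table 3.** The prospective aim reads "Development/validation of NEW/previous prognostic algorithms". The retrospective aim covers previous kinetic algorithms only and does not mention the new model.
- **Both segments as the basis of the new model.** The Discussion describes the new 90-day model as resting on retrospective and prospective data together. The Setting section adds: "for the development of the main algorithms, the study population will be utilized as a whole".
- **Centres in both segments.** Setting: "High-volume centers participating in the prospective segment will be allowed to enroll patients in the retrospective segment, too, voluntarily".

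The sample-size section opens by saying that the study was sized for both development and validation of prognostic algorithms.

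**The concern.** Which patients train a prediction model and which patients test it is the basic design choice for primary objective #2. The article makes that choice more than once, and the choices differ. An analyst could follow any of them and cite the protocol. Depending on the sentence followed, the reported performance would come from a model trained on a small prospective set and tested on retrospective data, from a model trained on everything with no separate test set, or from a prospective test of a model developed elsewhere. A reader of the results could not tell which split had been planned, and the split could be settled after the data are seen.

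The stated basis for 750 patients is a validation criterion. If those 750 are the development set, that basis says nothing about whether they are enough.

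**Working it through.** **1. The plan's own figures reproduce.** Inputs from the sample-size section: AF incidence p = 0.06, n = 800 in the calculation, n = 750 planned.

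- SE of ln(O/E) = √[(1 − p)/(n·p)]. For n = 800: √(0.94/48) = 0.140, as stated. For n = 750: √(0.94/45) = 0.145.
- 95% interval for the incidence = p ± 1.96·√[p(1 − p)/n]. For n = 750: 0.043 to 0.077, as stated. For n = 800: 0.0435 to 0.0765. So the stated SE belongs to 800 patients and the stated interval to 750, a small mismatch.
- AUC precision for 4000 patients (240 events, AUC 0.76, Hanley–McNeil standard error 0.0184): width 2 × 1.96 × 0.0184 = 0.072, as stated.

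**2. What these calculations cover.** The first concerns calibration in a validation set. The second appears under validation of L-GrAFT and EASE. Neither involves the number of candidate parameters, overfitting or shrinkage, so neither sizes the development of a new model.

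**3. Roles side by side.**

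| Source | New model developed on | New model validated on |
|---|---|---|
| Sample-size section, item 3 | not stated | prospective |
| Table 2, #2 and #3 | prospective | retrospective |
| Bias section | prospective, high-volume centres | medium-to-low volume centres |
| Table 3 | prospective | not assigned to the retrospective segment |
| Discussion | both segments | possible backward test on retrospective data |

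The rows cannot all hold for one model.

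**4. Expected 90-day events if development is prospective.** Events = 750 × incidence.

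- At the assumed 6%: 45.
- At 4% (lowest incidence cited): 30.
- At 11.1% (highest cited): 83.

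The missing-data rules exclude patients who died or were retransplanted before day 10 from algorithm development. The usable count is therefore lower, by a number the article does not give. No 365-day rate is given; the cumulative count at 365 days cannot be smaller than at 90 days.

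**5. Parameters that 750 patients support.** Patients per candidate parameter = 1/[(S − 1)·ln(1 − R²/S)], with target shrinkage S = 0.9 and R² the Cox–Snell value. R² is derived by assuming a normally distributed score with equal variance in failures and non-failures at 6% prevalence. The C-statistics are assumptions: 0.76 is the AUC in the plan's own calculation, 0.87 is the AUC it reports for EASE, and 0.80 lies between.

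| Assumed C | R² | Patients per parameter | Parameters in 750 |
|---|---|---|---|
| 0.76 | 0.053 | 165 | 4.5 |
| 0.80 | 0.073 | 118 | 6.3 |
| 0.87 | 0.120 | 70 | 10.7 |

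The range is about 5 to 11.

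**6. If both segments are pooled.** Development uses 750 + 4200 = 4950 patients, or 4950 × 0.06 = 297 expected events. The number is ample, but no patients are held out.

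**The case against.** Several counter-arguments have force.

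- **Table 3 can be read respectively:** develop new algorithms, validate previous ones. The validation label in the sample-size section might then refer to the existing scores only. That is plausible and removes part of the clash, but it leads to prospective development with about 45 events and no development sizing.
- **The Setting sentence may mean geographic pooling only.** It follows a contrast between Italy and other regions, so this is a natural reading. The Discussion is the better evidence for pooling segments.
- **Pooling does not rule out honest validation,** because resampling can provide it, and an article may leave that to the full protocol. This is fair. It does not explain why one segment is still called the validation set.
- **The 297 prospective data entries are not 297 candidate predictors.** They include identification, endpoint and follow-up fields, and Table 3 names four main parameters. For that reason no overfitting figure for a particular number of candidates is claimed here.

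A reader might infer that the new model must have either no independent validation or only a 45-event development set. The documents do not support so strong a claim. Taken alone, item 3 fits retrospective development with sound prospective validation, although no passage states this and objective #2 contradicts it. Prospective development also leaves the retrospective segment as a separate test set.

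A reader might also compute 15 + 56 − 60 = 11 centres in both segments. That does not follow: sixty is given as a minimum in Setting, Table 3 separates the segments by volume, and dual enrolment is voluntary. Overlap is possible, but its size is unknown.

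**Conclusion.** The concern holds as an unresolved contradiction about training and test data for a primary objective, together with a claim of development sizing that the calculations do not deliver. Unseen documents cannot excuse it, because the article itself assigns the roles and assigns them differently.

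The consequence depends on the reading. Prospective development rests on about 45 events and some 5 to 11 candidate parameters, conditional on 6% incidence, target shrinkage 0.9 and C between 0.76 and 0.87, and before early failures are removed. Pooled development has enough events but no held-out set. The finding does not show that independent validation is impossible, and it gives no figure for centre overlap. It must be settled before the new models are fitted.

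**What to change.** State one development set and one validation set for the new model. Align Table 2, Table 3, Setting, the bias section, item 3 of the sample-size section and the Discussion with that statement.

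**If development stays prospective, as objective #2 says:**
- Relabel item 3 and say that its O/E sizing concerns the existing scores only.
- Cap the candidate parameters in advance at what about 45 events support, with penalised estimation and bootstrap optimism correction.
- Validate on the retrospective segment for predictors recorded in both, and add this aim to Table 3.
- Remove or restate the claim that the sample size covers development.

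**If the segments are pooled:** use internal–external cross-validation, leaving out one centre or country at a time, and call neither segment a validation set.

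Where a separate validation set is kept, also report validation restricted to centres that did not contribute to development, since high-volume centres may enrol in both segments.

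The cost is fewer candidate predictors and some additional analysis and editing. No extra patients are needed. Moving development to the retrospective segment would be a redesign that reverses objective #2, and this point does not require it.
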